[figure not shown]

### Trial Summary

**Background:** Whilst breastfeeding is the desired feeding outcome for preterm infants, little is known about the development of preterm breastfeeding skills and the impact of bottle-feeding teats, nipple shields and degree of breast fullness on the achievement of full oral feeding. At King Edward Memorial Hospital (KEMH), there are limited rooming-in facilities for mothers of preterm and sick infants who may remain inpatients for up to 16 weeks. Mothers try to visit daily but distance, family and work commitments may limit this and mothers are rarely able to be in the neonatal intensive care unit (NICU) for all of their infant's suck feeds. Bottle feeds are required occasionally. There is evidence that an intraoral vacuum-triggered teat (Calmita, Medela AG) encourages a sucking action similar to breastfeeding and reduces the length of hospital stay and formula use at discharge compared to a conventional teat. We wish to examine the effects of different teats and breastfeeding support on feeding outcomes.

#### Objectives:

1. To track maturation of intraoral vacuum, SSB coordination and physiological stability over time and determine if this is related to increased breastfeeding effectiveness and efficiency.
2. To explore the effect of breast fullness on milk transfer at 34 weeks corrected gestational age (CGA).
3. To explore the use of a nipple shield on milk transfer at 35 weeks CGA.
4. To compare SSB coordination and maturation during breastfeeding with that during bottle feeding with Calmita, and bottle-feeding with a conventional teat.
5. To determine the effect of a vacuum triggered teat on timing of achievement of full breastfeeding and on breastfeeding duration

#### Trial Plan:

A randomised controlled trial of 60 preterm infants will be carried out. When an infant is ready for a suck feed but mother is unable to be present, bottle feeds will be given using a conventional teat (control group) or Calmita teat (intervention group). Weekly breastfeeds and bottle-feeds will be monitored for SSB coordination, heart rate, oxygen saturation and milk intake. Infants will have a single breastfeed monitored at 33 weeks CGA, and up to 2 breastfeeds monitored over 2 consecutive days at 34 weeks CGA (breastfeeds from 'full' and 'empty' breasts) and at 35 weeks CGA (with and without a nipple shield). The intervention group will be given the Calma teat (term version of Calmita) at discharge from the study hospital.

Breastfeeding outcomes will be tracked by follow up phone calls up to 3 months post term.

## Background

Whilst breastfeeding is the ultimate feeding outcome, breastfeeding duration is significantly shorter for infants born < 34 weeks gestation [1]. Little is known about the development of breastfeeding skills in hospitalised preterm infants. Further while achievement of full oral feeding is usually a requirement for discharge from hospital, the impact of different bottle-feeding teats on its timing is not clear. It is assumed that the removal of small milk volumes from the breast is due to low intraoral vacuums and immature suck-swallow-breathe (SSB) coordination however the influence of factors such as fullness of the breast, and the use of nipple shields, and different bottle-feeding teats have not been well investigated.

### *Maturation of preterm infant SSB coordination during breastfeeding*

Suck-swallow-breathe coordination is one of the most complex tasks required for safe and efficient feeding. Preterm infants often lack the maturity required for effective coordination and this is a major impediment to swift progression of oral feeding. No studies have precisely described the temporal relationship of SSB coordination nor have they investigated maturation of SSB coordination during the establishment of breastfeeding. Some data exists for bottle-feeding however direct translation is impossible due to the various study teats used, and differences in milk delivery with dissimilar oro-motor movements between breast and bottle-feeding. A study of bottle-fed preterm infants tracked from 34 through to 42 weeks CGA showed that effective SSB coordination is reliant on two factors; a consistent suck-swallow ratio of 1:1 or 2:1 and timing of the swallow during a safe point in the respiratory cycle ie. at the beginning of either inspiration or expiration [2]. Further significant maturation of feeding behaviour has been observed between 33 and 36 weeks CGA in a cohort of infants born at 28 to 31 weeks gestation[3]. Nipple shields may be employed to facilitate the preterm infant's attachment to the breast and improve milk transfer. This practice is based on the work of Meier et al.[4], however there are no standard guidelines for the implementation and transitioning from nipple shield use. Given that full breastfeeding would be the best possible outcome for these infants in terms of both short and long-term health very little basic research exists as a foundation on which to build effective clinical protocols.

### *Effect of delivery of milk via different teats on SSB co-ordination in preterm infants*

For preterm infants who have demonstrated the ability to attach and suck at the breast, in the absence of the breastfeeding mother it is common for some intra-gastric tube feeds to be replaced with bottle feeds with the rationale that more frequent suck feeds accelerate the progression to full oral feeding. This translates to the situation where it is rare for an infant not to receive a bottle during their hospital stay. One of the problems associated with bottle-feeding using conventional teats is the occurrence of apnoea, which is more frequent than with breastfeeding. Most recently we have shown that when hospitalised preterm infants are fed with a teat that does not release milk unless the infant creates a vacuum (Calmita, Medela AG, Switzerland), a sucking action similar to breastfeeding is facilitated, and this is

associated with improved breastfeeding rates at discharge and decreased length of hospital stay when compared to infants fed with a conventional teat. The incidence of any breastfeeding at discharge was similar between the groups (*Simmer et al, Novel feeding system to promote establishment of breastfeeds after preterm birth: a randomised controlled trial. Submitted*). It is possible that use of the Calmita teat facilitates coordination of SSB by the infant's regulation of milk flow. If so one would expect a reduction in apnoea and bradycardia during feeding with Calmita compared to the conventional teat. Further after discharge many preterm infants continue to require top up feeds from a bottle while transitioning to full breastfeeding. As the Calmita teat was not available following discharge from hospital it was not possible to determine whether continued use a vacuum controlled teat such as the Calmita or Calma (Medela AG, Switzerland) for top up feeds post discharge influences duration of breastfeeding and achievement of full breastfeeding

### Trial Aims

1. To track maturation of intraoral vacuum and SSB coordination as well as physiological stability of breastfeeding preterm infants over time and determine if this is related to increased effectiveness and efficiency of breastfeeding. We hypothesize that improvement in breastfeeding efficiency (mL/min) and effectiveness (total mL transferred) will be associated with changes in one or more of vacuum strength (average and changes across a feed), consistency of sucking (number of sucks/suck bursts per feed) and SSB coordination.
2. To explore the effect of the volume of milk in the breast on milk transfer during breastfeeding at 34 weeks CGA. Our hypothesis is that more milk in the breast will result in a higher volume of milk being transferred by the infant at the breastfeed.
3. (Optional) To explore the effect of nipple shield use on milk transfer at 35 weeks CGA. The hypothesis is that nipple shields improve attachment and breastmilk transfer
2. To compare SSB coordination and maturation during breastfeeding with bottle feeding with a Calmita teat, and bottle-feeding with a conventional teat. Our hypothesis is that infants fed with a Calmita teat will experience less apnoea and bradycardia and reach full oral feeds more rapidly than those fed with a standard teat.
3. To determine the effect of a vacuum triggered teat (Calmita during stay in study hospital, and Calma used for top up feeds post discharge/transfer from the study hospital) on the timing of achievement of full breastfeeding and on breastfeeding duration.

### Trial Design

#### Trial endpoints

The primary endpoint for this trial is total breastfeed volume (mL) transferred at a breastfeed, measured at 33, 34, 35 weeks and term CGA

Secondary endpoints to be measured during monitored feeds are  
efficiency (mL/min)

- total suck duration

- total suck bursts
- mean, peak and baseline intraoral vacuum (mmHg)
- oxygen saturation range
- heart rate range
- incidence of bradycardia
- incidence of oxygen desaturation

The following feeding endpoints will also be determined

- timing of achievement of full oral feeds
- timing of achievement of full breastfeeding
- breastfeeding duration (monitored up to 3 months post-term)

1. A randomized controlled clinical trial will be undertaken with random allocation in blocks of size 4 to either a control group or an intervention group. Study design is depicted in Figure 1.
2. A pilot study of up to 5 infants will be completed prior to commencement of the trial to test and refine the set-up and duration of monitoring sessions.
3. Study participant data and milk samples will be re-identifiable, with an identification code assigned to each infant. A master sheet that matches infant identity to identification codes will be stored in a password-protected electronic file on a lap top computer. All paper copies of case report forms will be stored in a locked filing cabinet at The University of Western Australia.
4. The effect of a vacuum-controlled bottle-feeding teat (Calmita and Calma teats, Medela AG) on breastfeeding outcomes will be evaluated in this clinical trial. A shut-off valve is incorporated into the Calmita teat so milk flows only when the infant creates a vacuum. Venting prevents collapse of the teat. There are two versions of Calmita with different threshold levels for the vacuum-controlled valve of  $-10 \pm 5$  mmHg (starter teat) and  $-30 \pm 15$  mmHg (advanced teat). We have previously investigated a prototype of this product but wish to carry out more extensive studies on the final product.

#### *Summary of findings from previous studies*

A randomised controlled trial of 97 preterm infants (birth gestation; Intervention:  $30^1 \pm 2^4$ ; Control:  $30^1 \pm 2^5$  weeks) was carried out at Special Care Nurseries (SCN) KEMH from August 1st to June 30th 2012 to compare Calmita with the conventional teat in use in the neonatal unit. Primary outcomes showed that time to full suck feeds were not different between the Control group and Intervention group (Calmita;  $p=0.24$ ). The Intervention group had shorter length of stay in hospital with a mean difference of 2.5 days for CGA at discharge ( $p=0.026$ ) and were discharged lighter. The Intervention group also received less formula at discharge (Intervention: 35%; Control: 16%,  $p=0.036$ ), but did not differ with respect to breastfeeding rates. It was concluded that use of Calmita during establishment of breastfeeding reduced duration of hospitalisation of preterm infants.

*Simmer K, Kok C, Nancarrow K, Hepworth AR, Geddes DT. Novel feeding system to promote establishment of breastfeeds after preterm birth: a randomised controlled trial. Journal of Paediatric and Child Health (under review).*

**Criteria for termination of the trial:**

Individual participants. Infants that demonstrate physiological instability ie. oxygen desaturations / bradycardia that require intervention (supplemental oxygen, or bag and mask ventilation) during a monitored study feed, where there have been no other episodes in the previous 24 hours, will be referred for review by clinical staff and advice sought re whether the infant should be withdrawn from the trial.

Entire trial: Safety of the trial will be monitored continuously and formally reviewed at interim analysis ie. at recruitment of 15 infants to each arm of the study to determine whether any adverse events have been reported as a result of monitoring or use of the trial teat. In that case, the trial will be stopped while the events are fully investigated, reported to WNHS Ethics Committee, and continuation of the trial re-considered.

We do not anticipate any adverse effects of the vacuum-triggered trial teat as data from our previous study indicates no change in physiological stability during its use of whereby, unlike a conventional teat, milk flow is controlled by the infant during feeding.

5. The expected duration of the trial is 12 months. The total duration of participation of mothers and infants is up to 43 weeks including intermittent monitoring over 3 weeks during hospitalization, one study site visit (likely to coincide with a scheduled hospital follow-up visit) and up to 3 follow up phone calls following discharge from the study site.

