## Treatment of Participants

1. When the mother is not available to breastfeed, control group infants will use a conventional teat for suck feeds whereas the interventional group infants will use the Calmita teat. The starter teat will be offered initially and when the infant takes full feeds from the starter teat for 48-72 hours they will then use the advanced teat.
2. Monitoring of a weekly breastfeeds and bottle feeds with the allocated teat will be performed at 33, 34 and 35 weeks CGA and involves the following
  - Weigh infant pre and post breastfeeding
  - Intraoral ultrasound
  - Continuous Intraoral vacuum measurements
  - Respiratory Inductive plethysmography
  - Continuous pulse oximetry for oxygen saturation (SaO2) and heart rate
  - (optional) Maternal pre/post breastfeed milk samples <1.0mL
  - Maternal rating of Preterm Infant Breastfeeding Behavior Scale[5] (PIBBS, Appendix A)

SSB coordination is evaluated using data from intraoral vacuum, respiration and swallowing (Respiratory Inductive Plethysmography) heart rate and oxygen saturation obtained throughout the entire breastfeed[6].

3. Test weights of the infant pre and post feed, for all feeds, will be made to determine milk intake and allow calculation of top up feeds. For monitored feeds, pre and post feed milk samples (<1.0mL) will be collected and fat content measured to provide a further estimate of breast fullness.
4. At each monitored breastfeed the Preterm Infant Breastfeeding Behavior Scale[5] (PIBBS, Appendix A) will be completed by the mother.
5. In the study setting it is assumed that most stable preterm infants are offered (at least daily) breastfeeding experiences from 32 weeks CGA. A weekly breastfeed will be monitored from 33 weeks CGA. At 34 weeks CGA each infant will have up to 2 breastfeeds and one bottle-feed monitored in random order on 2-3 consecutive days with a full or empty breast. A full breast is one that has not been expressed for 3 hours prior to feeding and an empty breast one that has been expressed within an hour of the feed. At 35 weeks CGA those using a nipple shield will have the option of also having a monitored breastfeed without a nipple shield.
6. At 35 weeks or at discharge/transfer each infant will have 1 breastfeed monitored with or without a nipple shield depending on whether the infant is typically feeding with a shield, and one bottle-feed will be monitored. Infants

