that remain in the Neonatal Nursery beyond 35 weeks CGA will be invited to continue with weekly monitored breastfeeds and bottle feeds until the time of transfer or discharge.

7. Each week the mother will be given the option of collecting a small milk sample (0.5-1.0mL) before and after every pumping or breastfeed over a 24-hour period to allow more accurate estimation of breast fullness. We expect milk production to increase over the study period therefore one 24-hour collection will not be sufficient.
8. Prior to discharge each mother will be asked to record expression volumes and the milk transfer at the breast (test weigh as in point 5) for a 24-hour period. This will be compared to the normal term infant ranges for 24 hour milk production/milk transfer.
9. At discharge/transfer the mother in the intervention group will receive Calma (term) teats to use for top up feeds while establishing breastfeeding.
10. The mother and infant will be invited to return to KEMH at term corrected age for monitoring of SSB during a breastfeed

The researchers will monitor compliance with use of the allocated teats and pre-post feed weighing during participants' hospital stay, and will be responsible for providing Calma teats to the intervention group mothers prior to the infants' transfer or discharge from KEMH.

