### Assessment of Safety

There are no foreseeable risks to the infant or mother. We do not anticipate any adverse effects of the vacuum-triggered trial teat as data from our previous study indicates no change in physiological stability during its use whereby, unlike a conventional teat, milk flow is controlled during feeding. To ensure safety, the incidence of apnoea and bradycardia, and any other adverse effects, will be recorded at each feed and examined at interim analysis when complete data is available for 15 infants in each group.

An expected benefit of study participation is better infant growth (in both infants fed with the conventional teat and those fed with Calmita) because breastmilk transfer will be measured for every breastfeed and top up feeds calculated to meet the volume prescribed by the neonatologist. Currently top up feed volumes are estimated based on assumptions about the volume taken at the breast – data from our previous studies indicate that the assumed volume is frequently overestimated. Mothers in this study may also be encouraged to continue breastfeeding simply due to the monitoring and follow up over the course of the study, whereby breastfeeding duration is tracked; this may result in longer breastfeeding duration.

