### Bottle feed

☐ Calmita starter    ☐ Calmita advanced                      ☐ Conventional

Pre feed weight:                      Pre feed milk sample                      ☐

Post feed weight:                      Post feed milk sample                      ☐

Total volume transferred:

Heart rate range:

SaO2 range:

☐ Resp plethysmography

☐ Intraoral vacuum

☐ PIBBS completed by mother

PIBBS score: \_\_\_\_\_

☐ 24hr production and milk samples collected    Result \_\_\_\_\_mL

Total number of feeds in last 7 days: \_\_\_\_\_

Total number of oral feeds: \_\_\_\_\_

Of these, total breastfeeds: \_\_\_\_\_

**Adverse events** – details eg. bradycardia, apnoea, interventions required

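### The individual safety referral rule misses events at unmonitored teat feeds and repeat events on the teat, and it does not separate stopping the teat from leaving the trial

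*Combined protocol and SAP*

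**What the plan says.** The rule for individual infants is in Trial Design, under the criteria for termination. It concerns desaturation or bradycardia needing supplemental oxygen or bag-and-mask ventilation, and it applies to events "during a monitored study feed, where there have been no other episodes in the previous 24 hours, will be referred for review" by clinical staff, with "advice sought re whether the infant should be withdrawn from the trial". No other section sets a trigger for an individual infant.

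Other safety provisions work at a different level:
- **Whole trial (same section).** Safety is watched continuously and reviewed formally at the interim, to establish "whether any adverse events have been reported as a result of monitoring or use of the trial teat". If so, the trial pauses for investigation.
- **Assessment of Safety.** Apnoea, bradycardia and other adverse effects "will be recorded at each feed and examined at interim analysis".
- **Oxygen saturation and heart rate monitoring.** Unit policy keeps infants below 34 weeks on continuous monitoring. Infants who no longer need it get oximetry for the monitored feeds.

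On exposure, Table 1 has the allocated teat in use for the whole nursery stay whenever the mother is away. Table 1 and Treatment of Participants schedule one monitored bottle feed in each of weeks 33, 34 and 35, then weekly by invitation. The statistical section specifies intention to treat.

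**The concern.** The question is whether the rule reaches the feeds at which the study teat could do harm. There are three gaps.

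1. **Scope.** An event needing oxygen at an unmonitored teat feed does not formally raise the question of whether that infant should stay on the teat.
2. **Window.** Screening out infants with background instability is sensible, because a monitored feed adds a tube, an ultrasound probe and bands. But the clause makes no exception for an earlier episode on the teat itself, so a repeat event on the teat can be screened out by the first one.
3. **Consequence.** The rule names only withdrawal from the trial. The plan does not say whether weighing, the term visit and the calls then continue. If they stop, an infant who reacts badly to a teat is lost to an analysis that is meant to include every randomised infant. The loss could differ by arm, since Trial Aims hypothesises less apnoea and bradycardia with Calmita.

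**Working it through.** The plan gives no coverage figure to reproduce. The check is a count, followed by a reading of the rule against cases.

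**Share of teat feeds outside the trigger**

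Inputs: m = 1 monitored bottle feed a week (Table 1; Treatment of Participants, items 2, 5 and 6). n = allocated-teat feeds a week, which is not stated and is therefore varied.

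Formula: share outside = 1 − m/n = 1 − 1/n.

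| n a week (assumed) | Outside the trigger | Over three weeks |
|---|---|---|
| 1 | 0% | 0 of 3 |
| 2 | 50% | 3 of 6 |
| 3 | 67% | 6 of 9 |
| 7 | 86% | 18 of 21 |
| 14 | 93% | 39 of 42 |
| 28 | 96% | 81 of 84 |

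Appendix E's 3-hourly or 2-hourly schedule caps feeds of every kind at 8 × 7 = 56 or 12 × 7 = 84 a week. The Trial Summary points both ways on n: bottle feeds are described as occasional, yet mothers are said to be rarely present for every suck feed. The budget section allows 30 + 60 = 90 Calmita teats per infant. Feeds per teat are not given, so this is only an indirect pointer to n. The trial will be able to measure n, because beside "Total number of feeds in last 7 days" the monitored-feed form counts oral feeds and breastfeeds, and their difference is bottle feeds. After 35 weeks, if the invitation to monitoring is declined, m = 0 and every teat feed is outside.

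**The rule against cases**

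| Event needing oxygen or ventilation | Rule as written | Rule as proposed under the fix |
|---|---|---|
| Monitored teat feed, nothing in the prior 24 h | Referred | Referred |
| Unmonitored teat feed, nothing in the prior 24 h | Not referred | Referred |
| Unmonitored teat feed overnight, then the next day's monitored feed | Neither referred: the first is unmonitored, the second fails the window | Both referred |
| Monitored feed, with a background episode away from teat and monitored feeds in the prior 24 h | Not referred (sensible screen) | Not referred |

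The third row is the clearest defect: the infant with the repeat event is the one the rule passes over.

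**Cost of a full withdrawal**

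- Dropout allowance (statistical section): 30 − 24 = 6 per arm. Each full withdrawal uses 1/6 = 17% of it.
- The primary endpoint is measured at four times: 33, 34, 35 weeks and term. An infant withdrawn after the 33-week feed loses 3 of the 4, plus the 2, 6 and 12 week calls.
- Volume is the difference between pre-feed and post-feed weights (Infant milk intake). It can still be obtained after the teat, tube and bands are stopped.

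**The case against.** The strongest reply is that the rule covers the research procedure, and that ordinary care covers the rest. At an unmonitored feed, giving oxygen is already nursery care, and staff can change a teat without a trial rule. The conventional teat in the previous trial was the one in use on the unit, so control-arm teat feeds are probably close to usual care. For the trial teat, the whole-trial rule is not limited to monitored feeds. This stands as partial cover. But whole-trial review does not ask whether a particular infant should stay on the teat, and care at the cot does not ensure that the trial team looks at the event.

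Three stronger readings are tempting, and the documents do not support them.

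- **That events at unmonitored feeds go unrecorded.** The only adverse-event field on the forms shown ("details eg. bradycardia, apnoea, interventions required") is on the monitored-feed form. But Assessment of Safety plans recording at each feed. Two other planned all-feed activities have no form shown either: "Test weights of the infant pre and post feed, for all feeds, will be made" and "The researchers will monitor compliance with use of the allocated teats and pre-post feed weighing". A missing field therefore proves little.
- **That most teat feeds are outside the trigger.** This is true only from three a week upward, and weekly use is not stated.
- **That withdrawal is automatic.** The rule only seeks advice on it.

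It is also tempting to delete the 24-hour clause or to demand one event line per teat feed. Deleting the clause would refer infants with background instability. A line per feed would mean 60 × 3 × 7 = 1,260 lines at 7 teat feeds a week, or 60 × 3 × 28 = 5,040 at 28. It could not be assumed to sit on a weighing record, because Table 1 and Infant milk intake specify weighing for breastfeeds only.

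**Conclusion.** The point holds as a gap in the individual trigger and as a wording gap about withdrawal. As written, unmonitored teat feeds do not trigger referral, and neither does a repeat event on the teat within 24 hours. The share of teat feeds outside is 50% at 2 a week, 67% at 3 and 86% at 7. It rests on one monitored bottle feed a week and an assumed weekly use. These figures measure feed coverage, not missed harm: the documents give no event rate, so neither missed events nor extra withdrawals can be counted. The conflict with intention to treat arises only if follow-up stops at withdrawal, which the plan leaves open. This is a cheap improvement to a plan that already has partial safeguards.

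**What to change.** Make the three changes together, since wider referral without the second could add full withdrawals.

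1. **Trigger.** Reword along these lines: *An infant who needs supplemental oxygen or bag-and-mask ventilation for desaturation or bradycardia, at a monitored feed or at any feed with the allocated teat, is referred to clinical staff for review, unless another episode occurred in the preceding 24 hours. An episode that itself happened during an allocated-teat or monitored feed does not count as another episode.* Clinical thresholds stay with the investigators.
2. **Consequence.** Replace withdrawal from the trial with being taken off the allocated teat, the monitoring equipment, or both. Unless consent is withdrawn, continue the scheduled breastfeed test weights at 33, 34 and 35 weeks, the term visit (a test weight at least) and the calls at 2, 6 and 12 weeks. Analyse the infant in the allocated arm, and state that a test-weighed breastfeed without the equipment counts towards the primary endpoint.
3. **Recording.** Record intervention-requiring events at unmonitored teat feeds by exception, in both arms. This carries out what Assessment of Safety already plans, without a line for every feed.

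The cost is two wording changes, a few more clinical reviews and a little event recording. No visits or procedures are added.
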